## Abstract

**Background:**

The evidence-based interventions of exercise and education have been strongly recommended as part of prominent clinical guidelines for hip and knee osteoarthritis (OA) for more than ten years. Despite the wealth of strong evidence that exists, implementation in practice is sub-optimal. This paper describes the key methodologies used in the co-design, tailoring, and evaluation of the IMPACT project implementation strategies, to confront this problem across multiple levels (micro, meso, macro) in public and private healthcare settings in Ireland.

**Methods:**

Using a type III hybrid implementation-effectiveness design, a participatory, dynamic and iterative process will be used to tailor and evaluate multi-level implementation strategies using the following stages: 1) Co-design the implementation strategies with key stakeholders using best evidence, a theory-driven implementation framework (Consolidated Framework for Implementation Research), local context and expert consensus; 2) Pilot and evaluate the implementation strategies by training physiotherapists to deliver the evidence-based Good Life with osteoArthritis Denmark (GLA:D®) education and exercise programme using the implementation strategies, and conduct a mixed-methods process evaluation; 3) Adapt the implementation strategies based on implementation process evaluation indicators from stage two. The adapted strategies will be used for scale-up and sustainability in subsequent GLA:D® Ireland training programmes that will be rolled out nationally. Evaluation of effectiveness on patient and cost outcomes will continue up to 12 months post-programme delivery, using an online patient registry and pre-post design.

**Discussion:**

This implementation science project aims to use participatory health research to address a gap in management of OA across public and private healthcare settings. This research has the potential to change practice and promote a policy of exercise and physical activity referral for chronic musculoskeletal disease that utilises community engagement effectively and enacts change ‘together’, with involvement of researchers, decision-makers, clinicians and patients.

**Supplementary Information:**

The online version contains supplementary material available at 10.1186/s12891-022-05599-w.

## Background

Osteoarthritis (OA) is a leading cause of disability and one of the fastest growing health problems in the world. From 1990 to 2019, the prevalence has risen by 48% globally to 528 million people worldwide [1] and this increase is expected to continue due to population ageing and obesity epidemic amongst other factors [2]. Irish data from The Irish Longitudinal Study on Ageing (TILDA) suggests that patients with OA make significant more use of general practitioner (GP) and outpatient services than those without OA, at an annual cost of €13.6 million [3]. The highest proportion of direct costs of the disease are attributed to orthopaedic surgery and in-patient hospital stays, with smaller proportions accounted for by medications, physician visits, other health professional visits and diagnostic procedures [4]. Substantial indirect costs include productivity losses from absenteeism, presenteeism (disease-related loss in productivity that occurs even when the person is at work), premature death and early retirement (increased social welfare costs and reduced tax revenue) [4]. In Ireland, a two-tier public-private healthcare system (similar to that in Australia and, to a lesser extent, the UK) often results in inequities in access to care, and a greater burden and waiting time for those less able to pay for access to private health services. This is exemplified by the results of the Euro Health Consumer Index 2018, which saw Ireland place last of 35 countries, in terms of healthcare accessibility [5]. Access to public healthcare comes through GP referral, with 60% of the population (those without medical card or insurance) paying out of pocket on average €52 per GP visit and 75% of the population paying up to €144 per month for drugs as well as paying for other primary care services [6], creating an additional burden on those with long-term chronic disease.

Despite being a typical chronic disease characterised by long duration, current management practices for OA are best described as reactive and palliative [4]. Too much focus is on end-stage joint replacement surgery and pain-relieving procedures or medications in the interim, at a significant cost to society and the individual. There is increased recognition across healthcare organisations and the field of musculoskeletal pain, that the overuse of procedures, testing, and medications constitutes low-value care which strains the healthcare system and causes unnecessary stress and harm for patients [7, 8]. Ireland has substantial orthopaedic waiting list times that have recently been exacerbated by COVID-19 pandemic-related cancellations. As of July 2021, over 84,000 patients across Ireland were waiting for an orthopaedic outpatient appointment, with 45% of these waiting over 1 year. Yet, even in the absence of a clear complication, total joint replacement does not always provide relief: up to 30% of total knee replacement patients remain dissatisfied with their surgical result after 1 year [9]. With the projected growth and cost of this disease, the sustainability of this health-care model is questioned. OA should be viewed as a chronic condition, where prevention and early comprehensive care models are the accepted norm, as is the case with other chronic diseases e.g. cardiovascular disease. A paradigm shift from tertiary to secondary prevention strategies in the form of early exercise intervention and education is required, in order to limit progression and minimise the health consequences of the disease.

Despite a wealth of strong evidence from over 60 randomised controlled trials (RCTs) [10, 11] and clinical guidelines [12, 13] supporting the efficacy of secondary prevention strategies such as exercise and education as first line treatment strategies for patients with painful knee and hip OA, implementation in clinical practice is suboptimal. An international meta-analysis on community care demonstrated that only 35–39% of patients with hip or knee OA received appropriate exercise recommendations or education/self-management options according to the guidelines [14]. Previous international programmes such as the Good Life with osteoArthritis from Denmark (GLA:D®) initiative have aimed to address this gap in care. This initiative is designed to support the implementation of guidelines for the treatment of hip and knee OA in clinical practice [15]. The programme consists of three main components: two to three sessions of evidence-based patient education, a six-week, twice-per-week physiotherapist-supervised neuromuscular exercise training programme, and patient registry to collect outcomes. Data from 9825 patients in the GLA:D® registry demonstrated improved pain intensity and quality of life at 3 months and 12 months after starting the programme [15]. Furthermore, physical function and physical activity improved, fewer patients took painkillers following the treatment (− 24%), and fewer patients were on sick leave due to their OA joint (− 44%) at 12 months compared with the year prior [15]. In addition, the programme has shown cost-effectiveness in primary care in Denmark, with healthcare costs per Quality-Adjusted Life Year (QALY) below conventional thresholds for willingness-to-pay [16]. Cross-cultural adaptation has proven feasibility, with results replicated across other countries such as Canada and Australia [17, 18].

Research highlights that the successful implementation of evidence into practice requires a comprehensive approach adapted to the translation of evidence into a specific setting with local stakeholders so that barriers to implementation in the local context can be understood and addressed [19, 20]. While previous research has highlighted the large number of barriers to implementation of OA interventions [21–23], the main challenge in this area today is to design and tailor actionable strategies that address these barriers. Implementation strategies are methods or techniques used to improve adoption, implementation, sustainment, and scale-up of interventions [24]. Strategies vary in their complexity and can be multi-faceted and influence multiple barrier levels. In the literature, limitations of implementation strategy development include inadequate identification of the contextual determinants (i.e. barriers and enablers) of implementation, little use of theory in designing or tailoring strategies and poor reporting of monitoring and evaluating strategies [25–27]. Applying the paradigm of participatory health research to implementation strategies has the potential to improve the uptake, adherence and sustainability of healthcare interventions. The goal of participatory health research is to maximise the participation of end-users in all stages of the research process. Research is not done “on” people as passive subjects providing “data” but “with” them to provide relevant information for improving their lives [28]. Some benefits of the participatory health research approach include explicit attention to culturally and logistically appropriate research, enhanced recruitment capacity, generation of professional capacity and competence in stakeholder groups, productive conflicts followed by useful negotiation, an increase the quality of outputs and outcomes, an increase in the sustainability of project goals beyond funded time frames and greater likelihood of system and policy changes [28]. This approach recognises the value of diverse stakeholders’ (patient/community members, clinicians, academics, health planners) contributions to the co-creation of knowledge in a process that is not only practical, but also collaborative and empowering [29]. It has been used successfully in Irish primary care implementation research before [30].

This protocol will describe the key methodologies used in the IMPACT project. IMPACT aims to use a participatory health research approach to co-design, tailor and evaluate implementation strategies to optimally implement an evidence-based exercise and education programme for hip and knee osteoarthritis in the Irish health setting.

## Methods

### Design, participatory approach and theoretical framework

A plain English language summary of this research can be found in Additional file 1. This research is defined as a hybrid effectiveness-implementation trial design (type III), which tests the ability of an implementation strategy to enhance use of an evidence-based intervention while collecting data on the health impact of the intervention during implementation [31]. Using a participatory health research approach, key stakeholders are supporting the co-design and evaluation of implementation strategies that will aim to embed an evidence-based programme for hip and knee osteoarthritis (GLA:D®) in the Irish healthcare system, across public and private settings. For the purpose of this project, a stakeholder is defined as anyone who is affected by or is involved in the development of and/or delivery of the research programme [28]. The four key criteria for meaningful involvement of stakeholders in participatory health research include identifying the research questions, sharing governance and decision-making, collaborative data interpretation and shared dissemination [28]. Accordingly, this research requires stakeholder input at each of these levels during each work package to ensure successful outcomes (described in detail below).

It is valuable to combine participatory health research with implementation theory because they offer a combined heuristic device to understand and support implementation processes [32]. The study is guided by the Consolidated Framework for Implementation Research (CFIR). The CFIR is a conceptual framework developed by Damschroder and colleagues to guide systematic assessment of multilevel implementation contexts (micro-meso and macro levels) and aid identification of appropriate expert-defined domains and constructs (individual characteristics, intervention characteristics, inner setting, outer setting, process) [33]. Used prospectively, the identification of these theoretical constructs can assist the researchers and contributors to pre-empt, or identify, factors that will positively or negatively affect the implementation of best evidence [34].

The evidence-based intervention that was selected for implementation of clinical guidelines for OA was the aforementioned GLA:D® initiative. This physiotherapist-supervised group education and exercise programme for hip and knee OA was chosen for the Irish context due to existing evidence of effectiveness [15, 18], the requirement of a patient registry to monitor outcomes and the success in adapting to other international and cultural contexts and healthcare settings (public and private) [17].

The SPIRIT 2013 checklist (defining standard protocol items for clinical trials) for this study is included in Additional file 2 and the Guidance for Reporting Involvement of Patients and the Public (GRIPP-2) checklist in included in Additional file 3. Ethical approval for this study has been granted by Galway Clinical Research Ethics Committee (REC) (C.A. 2685) and University of Limerick EHS REC (2020-12-13-EHS). For scale-up of the GLA:D® initiative in additional healthcare settings, distinct ethics permissions will be sought for each region where the programme is implemented.

To effectively implement clinical guidelines for OA in the Irish healthcare setting, the research methodology will involve three key inter-linked stages (Fig. 1):Co-design of implementation strategies,Pilot and evaluate the implementation strategies, andAdapt the implementation strategies for subsequent national rollout of GLA:D® Ireland.

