### STAGE 2: pilot and evaluate the implementation strategies

This stage will involve piloting the implementation strategies co-designed in stage one and evaluating the effectiveness of the strategies.

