#### Training of physiotherapists

An initial convenience sample of engaged physiotherapists will be contacted via word of mouth through co-investigators and steering committee members to take part in the first GLA:D® training course and pilot study. This sample will be representative of different regions and across private (small and large clinic) and public (primary care and orthopaedic hospital) healthcare settings in Ireland. These physiotherapists will participate in a 2-day continuous professional development course giving them the requisite skills to diagnose OA and deliver care as described in the clinical guidelines. The course theory summaries latest evidence on treatment of OA, as well as practical instructions in the specific protocol of GLA:D®, including delivering patient education, supervising and instructing neuromuscular exercise and the use of the online registry [15]. The course will initially be delivered by representatives from GLA:D® Denmark, with additional training on relevant implementation strategies identified in stage one provided by [name]. A patient representative will also be present at the training to provide appropriate input. This will give the physiotherapists access to an implementation ‘toolkit’ and online platform with all the material needed to deliver GLA:D® locally in the clinic.

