#### GLA:D® pilot programme delivery

GLA:D-trained physiotherapists (*n* = 8–10) will make use of existing or new referral sources to invite people with hip or knee OA to take part in the GLA:D® programme, as applicable for each setting. These sources include but are not restricted to clinic or orthopaedic waitlist, GP or other healthcare professional referral and self-referral. Eligible participants will have ‘joint problems from knee and/or hip that have resulted in contact with the health care system’. Exclusion criteria include non-OA cause of symptoms, e.g., tumour; inflammatory joint disease, or sequelae after hip fracture; other symptoms that are more pronounced than the OA problems, e.g., chronic, generalised pain, or fibromyalgia, acute knee trauma in the past 6 months or inability to understand the English language. The GLA:D® programme will comprise two to three education sessions and 12 (twice weekly) group neuromuscular exercise sessions as described in detail previously [15]. All group sessions will be supervised by a physiotherapist and can be delivered in a face-to-face or online format, as per clinician/patient preference and capability. Participants are encouraged to continue being physically active and to exercise, either with their physiotherapist or in their local community, to sustain the effects from the treatment in the long term.

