#### Evaluation of GLA:D® implementation

As established by Proctor and colleagues [41], a core set of implementation outcomes including: acceptability, adoption, appropriateness, cost, feasibility, fidelity, penetration and sustainability will be evaluated as outlined in Table 2*.* Implementation outcomes will be analysed descriptively using frequencies/proportions for categorical variables and means and standard deviations or medians and interquartile ranges for continuous variables.

**Table 2 Tab2:** Implementation outcomes and proposed method of collection

Outcome	Definition	Method of Collection (Level of analysis)
Acceptability	Satisfaction with various aspects of the programme	Survey on beliefs (Providers and patients); Survey on satisfaction at 3 months and 12 months post-programme (Providers and patients) Interview with providers: “Were you satisfied with the programme?” Interview with patients: “Were you satisfied with the programme?”
Adoption	Uptake and utilisation of the programme	Registry: Recording the number of referral sources, sites trained vs. sites implementing, trained physiotherapists and participant registrations from private and primary care settings (Providers and patients)
Appropriateness	Perceived fit, relevance, or compatibility of the programme for a given setting, provider, or consumer; and/or to address a particular issue or problem	Survey on beliefs (Providers and patients); Survey on satisfaction at 3 months post-programme (Providers and patients) Interview with providers: “How compatible is the GLA:D programme in your setting?” Interview with providers and patients: “Does the programme address a particular issue or problem?”
Cost	The financial impact of the implementation	Survey on barriers from WP1 (Providers and patients), Health utilisation and sick leave/medication use survey at 3 months and 12 months post-programme (Patients) Cost-effectiveness analysis Interview with providers and patients: “Have there been any cost implications?”
Feasibility	The extent to which the programme can be successfully used or carried out within a given setting	Collected with a survey at training course with strategies to overcome specific feasibility barriers discussed (Providers)
Fidelity	The degree to which the programme is implemented as it was prescribed in the original protocol	Interview with providers: “Did you make specific changes to the original programme? What did you change?”

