Implementation strategies are further operationalised by level i.e. micro, meso, macro. It is acknowledged that certain barriers may be non-modifiable within the scope and lifetime of this research study, particularly at a macro level. Nonetheless, strategies related to policy and engagement of stakeholders will work towards tailoring messages and driving change at these levels where appropriate. It is envisaged that patient outcomes and cost effectiveness data collected after 1 year of implementation will be used to leverage and advocate to Department of Health, the Health Service Executive and other relevant bodies to fund supervised exercise and education interventions for chronic musculoskeletal conditions. It will be important to apply this data alongside international evidence to help improve models of care and pathways for people with chronic hip and knee pain.

While local context is important to include with implementation efforts, this research has relevance beyond the specific setting in which it is being conducted. As with all intervention research, implementation strategies need to be fully and precisely described, in detail sufficient to enable measurement and ‘reproducibility’ of their components [24]. The details of the participatory health research process will be reported so that implementation projects work in other care settings, for other chronic conditions and other countries can be informed by lessons learned during that process. The use of theory in this study will also enhance the scope to accumulate knowledge about overcoming barriers to implementation [34]. Therefore, the strategies deemed to be effective will be published and shared widely for potential transfer and implementation in other healthcare settings, contexts and conditions.

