Dissemination activities arising from the results of this research will be co-planned and reviewed by the steering committee throughout the project. Annual reports, summarising evaluations on the effectiveness of the programme will be produced with accessible, lay terminology and infographics, and shared with clinicians and participants of the programme. Ensuring open access, these reports will also be available for free download on the GLA:D® Ireland website [47]. Sustainment of the GLA:D® Ireland initiative beyond the duration of project funding is one of the primary implementation indicators and will be addressed and tailored in implementation strategy design. The very nature of the implementation-effectiveness research design in this project will work to establish an evidence-based intervention within community healthcare settings. Nonetheless, it is critical that efforts to embed and sustain this initiative long-term are applied, through identification of the supports and processes required at micro, macro and meso levels. There is a clear need to identify and describe factors that affect sustainment outcomes in the field of implementation science, and a lack of evidence supporting discrete sustainment strategies for evidence-based interventions [48].

This research is limited by the pre-post design used to evaluate effectiveness of the intervention, without a comparative group. Since there are 100+ conclusive trials already completed in the area of exercise effectiveness for OA, the pre-post design was considered sufficient for the pragmatic monitoring of health outcomes in practice, alongside primary outcomes of implementation. This research may be subject to bias arising from the specific backgrounds and experiences of the researcher and steering committee members it is acknowledged, for example, that different group members may have prioritised or interpreted strategies and results in a different manner. Results of this research are also limited by the lack of available health administrative data to track healthcare usage in Ireland. However, using self-report, we can track use across private and public health services in this manner, that may not be feasible using health administrative data alone. This is important data to capture within a complex, two-tier system of care.

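### The plan sets out to evaluate whether the implementation strategies work, but one uncontrolled group of 8–10 engaged physiotherapists, analysed descriptively, can only describe implementation under them

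*Protocol article*

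**What the plan says.** **Purpose.** The section on design, participatory approach and theoretical framework places the study in the type III hybrid class, which "tests the ability of an implementation strategy to enhance use of an evidence-based intervention". The opening of Stage 2 states the purpose in the plan's own terms: "evaluating the effectiveness of the strategies". The Discussion describes patient health outcomes as being monitored "alongside primary outcomes of implementation".

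**Who is studied.** Under Training of physiotherapists, "An initial convenience sample of engaged physiotherapists will be contacted via word of mouth", by way of co-investigators and steering committee members. The next sentence begins "This sample will be representative of different regions" and goes on to list private and public settings. The number appears under GLA:D® pilot programme delivery: "GLA:D-trained physiotherapists (*n* = 8–10) will make use of existing or new referral sources".

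**What they receive.** The same training section describes a two-day course on the programme, with additional training on the Stage 1 strategies and access to a toolkit and online platform.

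**How it is analysed.** "Implementation outcomes will be analysed descriptively using frequencies/proportions for categorical variables", with means or medians for continuous variables. The α of 0.05 under Evaluation of effectiveness applies to patient change scores only.

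**What follows.** Stage 3 adapts the strategies for the national launch and re-evaluates them annually. The Discussion adds that "the strategies deemed to be effective will be published and shared widely". Its limitations paragraph names the missing comparison group for the intervention, not for the strategies.

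**The concern.** A claim that a strategy raises uptake needs some view of what uptake would have been without it. That could be sites not given the strategy, a period before it, or a rate fixed beforehand as the standard to beat. The article describes none of these for adoption, penetration or sustainability.

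If a pilot site starts the programme, at least three explanations are open: the standard course, the prior enthusiasm of a therapist chosen for being engaged, and the strategies. Nothing planned separates them.

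The consequences extend past the pilot. The strategies feed a national rollout and are offered for transfer to other settings and conditions, so readers may take them as tested. Engagement also bears directly on the primary outcomes. Uptake among people recruited through the project's own network is likely to flatter what later, openly recruited cohorts will show.

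**Working it through.** The article gives no sample-size calculation, adoption rate or margin for the implementation outcomes, so there is no figure to reproduce. The check is a comparison of passages, followed by illustrations in which every count and rate is assumed.

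**1. Claim against design**

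- *Claimed:* effectiveness of strategies, with implementation outcomes primary.
- *Groups:* one. No site is described as receiving the course without the strategies, and no staggering is described.
- *Baseline:* Table 2 lists numbers such as sites trained against sites implementing, and screened against participating. All are counted after the strategies are in use.
- *Benchmark:* none is described.
- *Per-strategy evaluation:* Co-design (Step 2) requires a method of evaluating each strategy's impact. The one worked example, Table 1, uses the number of sites trained and implementing plus interview feedback. That is an overall adoption count and cannot isolate the toolkit's contribution.
- *Later evaluation:* the annual review in Stage 3 describes no comparator either.
- *Stated limitation:* the Discussion justifies the lack of a comparator by more than 100 completed exercise trials. Those concern exercise, not newly co-designed implementation strategies.

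**2. Precision of a proportion among 8–10 providers**

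Exact (Clopper-Pearson) 95% limits for x of n: lower = 0.025 quantile of Beta(x, n−x+1); upper = 0.975 quantile of Beta(x+1, n−x). When x = n, the lower limit is 0.025^(1/n) and the upper limit is 1.

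- 6/8: 0.349 to 0.968, or 35–97%
- 8/8: 0.025^(1/8) = 0.631, or 63–100%
- 8/10: 0.444 to 0.975, or 44–97% after rounding from unrounded limits
- 10/10: 0.025^(1/10) = 0.692, or 69–100%

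These intervals treat providers as independent and ignore selection.

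**3. Would a benchmark rescue the pilot?**

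Take an assumed true adoption rate of 80%, an assumed benchmark p0, and the smallest x for which P(X ≥ x | n, p0) is at most 0.025.

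- n = 8, p0 = 50%: 8/8 is needed; α = 0.5^8 = 0.004; power = 0.8^8 = 17%.
- n = 10, p0 = 50%: at least 9/10 is needed; α = 11/1024 = 0.011; power = 10 × 0.8^9 × 0.2 + 0.8^10 = 38%.
- For p0 from 40% to 60%, power runs from 50% down to 17% with n = 8, and from 68% down to 11% with n = 10.

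A formal test would therefore seldom succeed at this size. Even a success would not attribute the rate to the strategies. This favours restating the claim over adding a test to the pilot.

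**The case against.** The strongest reply is that the design sentence is a definition of the hybrid class taken from the literature. On this reading the project's own aim is to co-design, tailor and evaluate through a mixed-methods process evaluation, for which descriptive analysis is right. No test or α is claimed for the strategies, and wide intervals are normal in a pilot. The pilot is also not the whole evaluation: each strategy is to carry its own evaluation method, annual review continues through the rollout, and sites still running are counted at 12 months and at project end.

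Much of this stands. Descriptive analysis fits a process evaluation, and the small sample is not an error. But the Stage 2 opening is the plan's own sentence, not a borrowed definition, and it promises effectiveness of the strategies. The per-strategy methods and annual reviews, as described, bring no comparator.

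A reader might infer four stronger points, which the article does not support:

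- *Unsuccessful strategies will be withheld.* The Discussion says that strategies judged effective will be published. It does not say that only those will be, and it also promises to report the process and lessons learned.
- *The sample is claimed to represent Irish physiotherapists.* The sentence concerns coverage of regions and settings, and the convenience sampling is disclosed.
- *Pilot adoption is an upper bound for the rollout.* Strategies are revised first, so later adoption could move either way. Likely optimism is as far as one can go.
- *Keep, adapt or drop values are wrongly missing.* They depend on strategies not yet co-designed when the article was written, and an article may leave such detail to the full plan.

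**Conclusion.** The point holds as a mismatch between claim and design. As described, the study can report how many engaged therapists adopted the programme, how feasible it was and what got in the way. It cannot show that any strategy, or the package, increased use, and the admitted limitation does not extend to the strategies. No calculation in the article is wrong.

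The size can only be illustrated: with 8–10 providers, a seemingly strong adoption result remains compatible with true rates from roughly 35–63% upwards (6/8, 8/10 and 8/8 as assumed counts), before any allowance for selection. That the strategies reach every pilot site together is inferred from the training section, not stated outright. With no comparator behind the judgement, singling out strategies as effective risks selective reporting. It does not establish that selective reporting is planned. The matter should be corrected because it changes what the study may conclude, and correction is cheap.

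**What to change.** 1. In the design section and the Stage 2 opening, state that the study describes implementation under the strategies, in place of testing or evaluating their effectiveness.
2. In the Discussion's limitations paragraph, say that the strategies too are evaluated without a comparison group, and that the existing exercise trials do not make up for this.
3. Report adoption and sustainability with exact confidence intervals, separately for the invited pilot cohort and for later training cohorts. Base national conclusions on the later cohorts.
4. In the Discussion's publication statement, commit to reporting the evaluation of every strategy, whatever the result.

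The cost is a more modest claim, some rewording and a few stratified tables. No new data collection is needed.
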